##### Sham TBS Protocol

The sham TBS treatment will be conducted with identical conditions of active TBS using a sham TBS coil. The sham coil has no difference in shape and appearance to that of the active coil except for an additional black coil sheath for reduction of the diffusion of magnetic fields. It delivers stimulation over only scalp skin and superficial muscles without proposed physiological modulation effects on the cortex (66).

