## Methods/Designs

### Study Design

This is a randomized, sham-controlled double-blind study. Participants will be randomly assigned by main investigator to three parallel groups using computer-generated random numbers with a 1:1:1 allocation ratio, either receive (1) MA-related cues retrieval in VR combined with active TMS (group A: MA VR scene + TBS) or (2) sham TMS (group B: MA VR scene + sham TBS), or (3) neutral cues retrieval in VR combined with active TMS (group C: neutral VR scene + TBS). Participants, outcome assessors, and data analysts will be blinded to the group assignment during treatment sessions. The doctors delivering TMS treatment will know the allocation sequence but will not be involved in the assessment. Once treatment is completed, participants will be asked to guess the specified intervention they have received to determine the actual effect of TBS. Then the clinical evaluator will debrief the participants about the study procedures. The two “VR retrieval–TBS” treatment sessions will be scheduled in 2 days within 1 week using an MA-related or neutral VR scene. Clinical, psychological questionnaires and EEG will be carried out at baseline (T0), each treatment session (T1/T2), the week of the last treatment (T3) and over 1 month after treatment (T4), as shown in Figures 1, 2. This protocol follows SPIRIT recommendations.

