##### Intensity Identification

The RMT is suggested as the minimal TMS intensity required to elicit motor evoked potentials (MEPs). It will be identified by flexion/extension movements of any finger, especially the index and little finger, in at least 5 of 10 consecutive MEPs trials (32). A single TMS session will be conducted by a figure-of-eight TMS coil following previous suggestions (64), with a gradual increase (5% each time) from 40% of median output intensity up to an intensity which could induce slight but significant finger movement. The coil will be applied over a suggested “finger motor cortex,” with a TMS-matched elastic cap. This location was examined about approximately 8–11 cm lateral and 0–4 cm anterior to the cranial vertex (65). Thus, the TMS provider should concern with both cap-provided “marker” and information about a relative position, to find the “hotspots” accurately.

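### As described, the sham coil looks different from the active coil (an added black sheath), so participant blinding in the active-versus-sham TBS comparison is not secured

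*Protocol article*

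**What the plan says.** The Study Design section makes the claim: "This is a randomized, sham-controlled double-blind study". It then names who is blinded: "Participants, outcome assessors, and data analysts will be blinded to the group assignment during treatment sessions". The operators are the stated exception: "The doctors delivering TMS treatment will know the allocation sequence but will not be involved in the assessment". After treatment, participants guess which intervention they received. The purpose given is to establish the actual effect of TBS; a check of blinding is not mentioned.

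The Sham TBS Protocol section describes the sham coil: "The sham coil has no difference in shape and appearance to that of the active coil except for an additional black coil sheath". The sheath is there to limit the spread of the magnetic field, so it is the part that makes the coil a sham. Of the sham stimulation the section says: "It delivers stimulation over only scalp skin and superficial muscles without proposed physiological modulation effects on the cortex". Other conditions are to be the same as for active TBS.

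The Intensity Identification section describes how the resting motor threshold is found: "A single TMS session will be conducted by a figure-of-eight TMS coil following previous suggestions", with output raised "up to an intensity which could induce slight but significant finger movement".

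**The concern.** A sham protects participant blinding only if the participant cannot tell it from the active device. Here the article's own description names a visible difference and attaches it to the sham coil alone. A participant who has already met an active coil may have something to compare it with.

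What is at stake is the comparison of group A (MA scene, active TBS) with group B (MA scene, sham TBS). The craving VAS and the anxiety, depression and mood scales are all rated by the participant. Someone who suspects a sham may expect and report less benefit, which would plausibly make active TBS look better. The Discussion hopes to show an effect on self-reported craving, and that is among the outcomes most open to this bias.

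**Working it through.** The point is not numerical, so the check sets the sections side by side.

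1. **Do the coils differ in appearance?** Yes, as written. The Sham TBS Protocol section equates shape and appearance and then makes one exception, the black sheath. No matching cover on the active coil is described, and nothing is said about hiding the coil from view.

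2. **Does every participant meet an active coil?** Yes, by firm inference.
   - A threshold above 50% of maximum output is a non-inclusion criterion (Participants), so everyone enrolled has been tested.
   - Pulse intensity is set from the individual threshold (Intervention), and sham runs under the same conditions as active TBS (Sham TBS Protocol).
   - The test ends at finger movement (Intensity Identification). A coil described as having no modulating effect on the cortex would not be expected to produce that.

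3. **Does the threshold coil look like the bare treatment coil?** Not stated. Intensity Identification gives only a figure-of-eight coil, with no model and no description. TBS Pattern names a model for treatment but does not say that the same coil is used for the threshold. The consequences differ:

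| Threshold coil looks like | A and C see at treatment | B sees at treatment |
|---|---|---|
| the unsheathed active coil | no change | a change (sheath) |
| some other coil | a change | a change |

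Only in the first row does threshold testing itself set B apart. In the second row the sheath still distinguishes the treatment coils, but the within-person cue is no longer specific to B.

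4. **Is there opportunity to see the treatment coil?** Some. It is held at Fp1, on the forehead (Target to Stimulate). There are two sessions, each with two trains and a 60-s break (TBS Pattern), and a short trial precedes full-length treatment (Intervention). Participants give feedback on coil movement, so they are attentive.

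5. **Which contrasts are exposed?** A versus B has the same scene and a different coil, so it is exposed and is the only contrast that changes TBS alone. A versus C has the same active coil and a different scene, so it is not exposed through the sheath. B versus C changes both coil and scene and isolates neither.

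6. **Would the planned guess catch it?** Only if unmasking is gross. As an illustration, reduce the guess to active versus sham, so that chance is 50%, and test one-sided at 0.05 with an exact binomial. The guess rates below are assumptions.
   - A and B together, n = 15 + 15 = 30: at least 20 correct are needed, since P(X ≥ 20 | 30, 0.5) = 0.049. Power is 0.29 if 60% truly guess right, 0.73 if 70% and 0.97 if 80%.
   - B alone, n = 15: at least 12 correct are needed, since P(X ≥ 12 | 15, 0.5) = 0.018. Power is 0.09, 0.30 and 0.65 at the same rates.

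The guess is worth reporting, but a non-significant result would not show that blinding held, and it comes too late to prevent anything.

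**The case against.** The strongest reply is that the route to unmasking is a chain of suppositions. The threshold coil is not described, and over the motor cortex it sits where the wearer cannot easily inspect it. Each participant receives one kind of treatment coil, and would have to notice the sheath, remember the earlier coil and infer that a sheath means sham. Viewing conditions may be settled in the full protocol. Skin and muscle sensation is addressed, a guess is planned, and the primary outcome is EEG power, not a rating.

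Much of this stands. It rules out three stronger readings that a reader might infer:

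- *That all 15 in B will see a different coil from the one at threshold testing, while none of the 30 in A and C will.* This needs the threshold coil to look like the bare treatment coil, and the article does not say so.
- *That anyone present, assessors included, can read the arm from the sheath.* No section places an assessor or analyst at coil delivery. The treating doctors already know the allocation and do not assess. The sheath could identify B but cannot separate A from C.
- *That participants will compare notes.* The article shows a single center and says nothing about contact among participants.

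The reply does not remove the stated difference in appearance. The article does describe the sham, and that description contains the problem, so condensation does not explain it away. Keeping the doctors out of assessment protects the assessment, not the participant's own belief about treatment.

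**Conclusion.** The point holds in limited form. As written, the coils differ in appearance, which does not secure the claimed blinding of participants in A versus B. That much rests on the article's own words. That everyone meets an active coil is a firm inference. That B alone could notice a change from threshold testing to treatment is conditional on the look of the threshold coil.

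The exposure is greatest for the self-reported secondary outcomes. It is smaller for the EEG primary outcome, although expectancy could still act there. A versus C is untouched. The document shows that unmasking is possible, not that it will occur. It gives no basis for sizing a bias, and the likely direction, in favour of active TBS, is an assumption about expectancy. This does not invalidate the design. It is a weakness in the key sham contrast that is cheap to remove.

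**What to change.** - Make the coil look the same to the participant in all three arms, at threshold testing and at treatment. Either fit the active coil with a matching outer cover that does not shield the field, or keep the coil out of the participant's view throughout.
- Amend the Sham TBS Protocol section to state which of these is done, and add a matching sentence to Intensity Identification.
- In Study Design, define the post-treatment guess as a check of blinding and report it by arm.

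The cost is a cover or a viewing arrangement plus a few sentences, with no added visits or staff. If a cover is used, it must be checked not to alter coil output, and the motor threshold must be measured with it on. Keeping the coil out of view avoids that downside.

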### Outcome Measures

#### Primary Outcome Measure

We will evaluate the short-term effects of Retrieval-TBS treatment in the reduction of cue-induced drug craving and cue reactivity by comparing EEG in VR scene between baseline (T0) and post-test (T3).

***EEG*** will be recorded by a portable EEG system (Muse by Interaxon Inc.) during each VR session (3 min/scene × 1 MA-related VR scene and 1 neutral-related VR scene = 6 min) at T0 and T3, respectively. Each patient will wear an EEG headset before entering the VR scenes. Four channels (refer to EEG 10-20 system: FP1, FP2, TP9, TP10) and an original reference (FPz) will be retained to measure the brainwave spectrum including delta, theta, alpha, beta and gamma (with a sample rate of 256 Hz and 12 bit resolution), frequency bands between 45 and 60 Hz were omitted because muse hardware applied notch filters at 50 and 60 Hz to reduce environmental noise (67). According to a previous study, there was a significant difference between drug-cue and neutral-cue-induced EEG activities (68). In terms of drug-cue related memory, the frontal theta activity used as a feedback signal in adaptive regulation was highlighted for memory updating (69), which has been suggested as an indicator of the enhanced binding of incoming interconnected information in memory formation (70), while the beta activity which reflects a memory promoting state (70) indicated the level of memory integration in reconsolidation (71). Since the wearable devices available in VR have been applied to classify emotional states (72), we plan to use wearable EEG combined with VR scenes to observe the brain activity associated with memory in the current study. The average power in EEG frequency bands (i.e., δ = 1–4 Hz, θ = 4–8 Hz, α = 8–13 Hz, β = 13–30 Hz, γ = 30–50 Hz) are real-time computed in hardware and sent alongside an indicator of data quality from each sensor. The Muse manufacturer provided on-device computed FFTs (https://sites.google.com/a/interaxon.ca/muse-developer-site/museio) were used to estimate the spectral power density (μV2/Hz) for frontal electrodes in each frequency band in this study. EEG spontaneous measures at the frontal sites were calculated, as shown in Figure 2, by 1 min post-dark data minus 1 min pre-dark data in each frequency band in each VR scene. We used state-related EEG to calculate the EEG activities for drug-related craving state in VR, because cue-induced craving is related to a tonic, slowly changing craving state and Muse is a portable device that may not stably acquire EEG activities during walking in VR scene. Previous studies have used “state-related EEG” to compare different EEG activities in different state (56, 72, 73). Because of the non-normal distribution, power density value and ratios were log-normalized. For statistical tests, a two-tailed alpha of 0.05 was used unless explicitly stated otherwise.

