#### Data Preparation and Descriptive Statistics

After inspecting original data, identifying unusual cases, transforming and summarizing data-sets according to different types of variables: the mean, median, standard deviation, ranges and valid samples will be required at first, as well as the counts and percentages specific for categorical variables. Firstly, running SPSS 21.0 for basic check of validated data both based on the extent of treatment completion (>85%) and accepted level of missing/obscure/contaminated data (<10–20%). The missing data will be estimated via multiple imputations. Secondly, the distribution of data will be analyzed both by stem-and-leaf plot (SPSS 21.0), the actual data calculated for normality overlay a normal curve will be required to determine that to what extent it is a normal distribution (without significance at given alpha = 0.05). For a poor fitted normal curve, non-parametric inferential will be selected, while the standard or similar standard alloy will run the parametric inferential.

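### The primary EEG measure is on-device band power from two forehead electrodes with no described rule for eye or muscle artefact, so non-cortical power can enter the theta and beta bands the protocol interprets

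*Protocol article*

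**What the plan says.** The Primary Outcome Measure section assesses the short-term effect "by comparing EEG in VR scene between baseline (T0) and post-test (T3"). It fixes how the EEG measure is obtained:

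- **Montage.** "Four channels (refer to EEG 10-20 system: FP1, FP2, TP9, TP10) and an original reference (FPz) will be retained". No eye-movement or muscle channel is listed.
- **Source of band power.** Average powers in five bands "are real-time computed in hardware and sent alongside an indicator of data quality from each sensor". The manufacturer's on-device FFTs "were used to estimate the spectral power density (μV2/Hz) for frontal electrodes in each frequency band in this study".
- **Filtering.** The only step named is that the "muse hardware applied notch filters at 50 and 60 Hz to reduce environmental noise".
- **Window.** The measure is calculated "by 1 min post-dark data minus 1 min pre-dark data in each frequency band in each VR scene". One reason given is that the "Muse is a portable device that may not stably acquire EEG activities during walking in VR scene".

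The same section reads frontal theta as a sign of memory updating and beta as a sign of memory integration. The Introduction puts forward raised prefrontal beta as a marker of craving. Data Preparation and Descriptive Statistics adds a general check for all data, an "accepted level of missing/obscure/contaminated data (<10–20" per cent). It is not specific to EEG.

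**The concern.** Fp1 and Fp2 lie above the eyes and over forehead muscle. It is general EEG knowledge, not a figure from the document, that blinks and eye movements at these sites add low-frequency power (delta and theta) and that muscle tension adds power in beta and gamma. Theta and beta are the bands given a memory or craving meaning here. Muscle tension after a drug scene would also push beta in the direction the Introduction associates with craving.

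At stake is what a positive or null primary result means. A positive result might partly reflect less blinking or a more relaxed forehead. A null result might reflect an outcome too noisy to show a cortical change.

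**Working it through.** **1. Which stated control deals with which source of contamination**

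| Source | Control in the article | Sufficient? |
|---|---|---|
| Mains noise | 50/60 Hz notch | Yes |
| Walking | Dark minutes analysed instead of the scene | Largely |
| Poor contact | Quality indicator per sensor | Unclear: no rule for its use |
| Blinks, eye movement | None described | No |
| Forehead muscle | None described | No |

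**2. Does the subtraction remove it?** Write measured band power as cortical power C plus artefact power A, a simplification that treats the two as additive. Then post − pre = (C_post − C_pre) + (A_post − A_pre). The second bracket is zero only if artefact is equal in both minutes. The scene between them is meant to raise craving, so equality cannot be taken for granted. Comparing T3 with T0 and then comparing arms removes whatever part of that bracket is constant over visits or common to the arms. What remains is random variation, plus any change that differs by arm.

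**3. Can it be corrected later?** From band-power summaries, flagged stretches can be dropped. Sample-level blink or muscle correction and re-referencing cannot be done, because the samples are no longer there. Both are possible if the raw signal is kept.

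**4. Size.** No figure in the document measures artefact, so the following is an illustration only.

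Inputs from Sample Size: f = 0.2496, three groups (k), four repeated tests (m), α = 0.05, power 0.95, N = 45. Assumed, because not stated: correlation ρ = 0.5 between repeated measures, and sphericity. The stated f is used as it stands. It comes from a craving outcome in another study, and the article's own formula gives √(5.65/96) = 0.2426, which is a separate matter.

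Within-between interaction: λ = f²·N·m/(1 − ρ), df1 = (k − 1)(m − 1), df2 = (N − k)(m − 1).

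- Plan's figure, m = 4: λ = 0.0623 × 45 × 4/0.5 = 22.4, df 6 and 126, power 0.955. N = 45 is reproduced.
- T0/T3 contrast, m = 2: λ = 0.0623 × 45 × 2/0.5 = 11.2, df 2 and 42, power 0.832.

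Suppose the stated f applied to a clean measure, and a share s of the observed variance is artefact unrelated to arm, with ρ unchanged. Then f becomes f·√(1 − s):

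| s (assumed) | f·√(1 − s) | Power, m = 4 | Power, m = 2 |
|---|---|---|---|
| 0 | 0.250 | 0.955 | 0.832 |
| 0.10 | 0.237 | 0.930 | 0.789 |
| 0.25 | 0.216 | 0.869 | 0.707 |
| 0.50 | 0.177 | 0.678 | 0.522 |
| 0.75 | 0.125 | 0.359 | 0.284 |

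**The case against.** **A condensed article may leave cleaning rules to a fuller document.** This is fair as far as it goes: the article shows that no rule is described, not that none exists. But it does more than stay silent. It names device-computed band power as the source of the endpoint, and a fuller plan that kept that source could not add sample-level correction.

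**The raw signal may already be kept.** The article says the four channels and the reference will be retained and gives a 256 Hz sampling rate, which may mean the samples are stored. If so, the fix is cheaper still, but the endpoint as written does not use them. A reader might infer that the data can never be cleaned. The documents do not support that.

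**Randomisation and blinding protect the comparison.** This stands. All arms use the same device, and artefact unrelated to arm adds noise without bias. A reader might infer that the primary result will be biased. Nothing in the document shows that eye or muscle activity will change differently by arm. The risk is to what the endpoint measures.

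**The reference.** A reader might go further and say that FPz, lying between Fp1 and Fp2, subtracts out the medial prefrontal signal of interest, and put a factor on the loss. Any factor needs the correlation between the sites, which the document does not give. The same subtraction also weakens symmetric blinks, which helps. And if the difference is taken on the log scale (the article log-normalises power, though the order of steps is unclear), a constant attenuation cancels. The choice of reference is a trade-off, not an error.

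**Conclusion.** The point holds in this form. As written, the primary EEG measure lets blink, eye-movement and forehead-muscle power into the bands it interprets, and no stated control addresses them. The consequences are added noise and a weaker claim that a group difference reflects cortical cue reactivity. Bias in the randomised contrast is possible but not demonstrated.

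The size is unknown. The power losses shown, such as 0.83 to 0.71 at a 25% artefact share, rest on assumed shares, ρ = 0.5, sphericity and the stated f. They show how sensitive the trial would be, not what will happen. The change should be made because it is cheap and cannot be made after recording if only the summaries are saved.

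**What to change.** - Save the raw 256 Hz signal from all four channels at every EEG visit. At 12 bits, one dark minute is 256 × 60 × 4 = 61,440 samples, about 92 kB, so storage is no obstacle.
- Compute band power offline, by someone blinded to arm, with rules fixed before unblinding: an amplitude limit for blinks and eye movement, a high-frequency limit for muscle bursts, exclusion of stretches flagged by the quality indicator, and a minimum number of clean seconds in each dark minute.
- Make this the primary EEG measure, with the on-device FFT as a sensitivity analysis.
- Re-reference to the mean of TP9 and TP10 as a sensitivity analysis only. It needs no new recording, because (Fp1 − FPz) − mean(TP9 − FPz, TP10 − FPz) = Fp1 − mean(TP9, TP10). It keeps more cortical signal but also more blink.
- Report clean seconds by arm, visit and window, so that a reader can see whether artefact differed.

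No new device, visit or staff is needed. The real cost is data: each window is only 60 seconds, some epochs will go, and a few participants may fall below the minimum. With 15 per arm that matters, so the minimum should be set with the expected loss in mind, and the handling of those participants stated in advance.

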The purpose of this protocol is to design a set of clinical treatments to obtain a sustainable inhibitory effect on the craving for MA after a limited number of interventions. We propose that TMS stimulation of the OFC within the time window of MA-related episodic memory reconsolidation will produce a continuous reduction in craving elicited by MA-related cues or context. In specific, we will use theta-burst stimulation (TBS), a new pattern of TMS, to modulate the activity in the OFC because of its advantage for stronger effects with shorter duration compared to conventional repetitive TMS (40). We will choose continuous TBS (cTBS) due to its promised effect on depression of cortical excitability (22, 31, 33). It has been delivered to the medial prefrontal cortex to decrease reactivity to alcohol-related cues and reduce drinking behavior in a recent studies (39). And cTBS has been used to disrupt OFC network activities in previous studies (41). Since an effective activation of episodic memory is important in reconsolidation-based treatment (42, 43), a series of vivid and immersive VR scenes related to MA using will be present for memory retrieval and craving self-rating (43–45). In addition to self-report craving, the cue-related electroencephalogram (EEG) activity in the VR scene will be recorded as an indirect measure of the degree of memory retrieval and craving (43, 46, 47). Compared to neutral scenarios, the incentive salience of drug-related cues is stronger to draw drug user's attention (48, 49). Attention bias for drug-related cues is associated with subjective craving and tendency to approach drug-related cues (50, 51), indicated by abnormal EEG activities of prefrontal cortex. For example, two studies reported that MA users showed specific EEG features induced by MA-related scenes presented by VR, such as decreased gamma activity in OFC and right DLPFC (52) and reduced EEG power in delta, theta, and alpha bands (53) comparing to neutral scenario. In addition, processing alcohol- or smoking-related cues coincided with surged frontal beta-band activity in binge drinkers (54) or smoker (55); the increased beta-band activity in response to the drug-related cues is associated with enhanced attention and alertness. A recent study further showed that a higher level of synchronization of medial prefrontal cortex for the beta-band activity in 1–3 months abstinent MUD group, compared to groups with longer or shorter abstinence. Meanwhile, MA craving was higher in the 1–3 months abstinence group than other groups (56). This finding suggests that increased prefrontal beta activity may serve as a robust indicator of MA craving.

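### The primary EEG outcome covers five frequency bands under a blanket two-sided 0.05 with no primary band, site summary or multiplicity rule, while the sample size assumes one test

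*Protocol article*

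**What the plan says.** The section Primary Outcome Measure defines the outcome as a short-term effect assessed "by comparing EEG in VR scene between baseline (T0) and post-test (T3"). No band is named there. The section then lists the recording sites, "Four channels (refer to EEG 10-20 system: FP1, FP2, TP9, TP10"), and the bands, "δ = 1–4 Hz, θ = 4–8 Hz, α = 8–13 Hz, β = 13–30 Hz, γ = 30–50 Hz". Spectral power is estimated "for frontal electrodes in each frequency band in this study". The derived measure is the post-dark minute minus the pre-dark minute, for every band and scene, after log transformation. The section closes with "For statistical tests, a two-tailed alpha of 0.05 was used unless explicitly stated otherwise".

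Inferential Statistics compares EEG and ECG between the three groups by paired t-test or a group by time ANOVA (baseline, post-test), or by non-parametric alternatives. It does not restrict the analysis to a band.

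Sample Size plans a 3 × 4 repeated measures ANOVA for one interaction test at α = 0.05 with power 0.95 (printed as β), giving 45 participants.

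On gamma, the same outcome section says "frequency bands between 45 and 60 Hz were omitted because muse hardware applied notch filters at 50 and 60 Hz" and, a little later, "γ = 30–50 Hz) are real-time computed in hardware".

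**The concern.** The variable that decides a trial belongs in its protocol. Here the device, sampling rate, band limits and alpha are given, but not which of the five band powers is decisive. The only alpha rule is a general default applied to each test. Followed as written, a difference in any of five bands could be reported as a positive primary result, so the chance of at least one false positive would exceed the 5% on which the sample size rests.

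Interpretation suffers too. For drug cues the Introduction cites lower gamma, delta, theta and alpha but higher beta, and the outcome section stresses theta and beta. A reduction in cue reactivity would therefore mean a rise in some bands and a fall in another. The three-group F test carries no direction of its own.

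**Working it through.** **Inputs from the protocol article.** Two-sided α = 0.05 per test; 5 bands; 2 frontal channels among the 4 recorded (FP1, FP2), with no statement on whether they are averaged; 3 groups of 15; f = 0.2496 as printed; target power 0.95; four time points in Sample Size and two in Inferential Statistics.

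**Assumed, because the article does not give them.** Correlation between bands, 0 to 0.9; correlation between the two frontal sites, 0.5 to 0.9; correlation between repeated measures ρ = 0.5; sphericity.

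**1. The plan's own sample size.** For the within-between interaction, λ = f²·N·m/(1 − ρ), with df (k − 1)(m − 1) and (N − k)(m − 1). With k = 3, m = 4 and N = 45, λ = 0.2496² × 45 × 4 / 0.5 = 22.43 with df 6 and 126, and power is 95.5%. At N = 42 it is 93.8%. So 45 is reproduced, for one test at 0.05. (The printed formula applied to F = 5.65 with df 1 and 96 gives √(5.65/96) = 0.2426, not 0.2496. That is a separate matter; the printed f is used here.)

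**2. False-positive risk with independent tests.**
- Five bands: 1 − 0.95⁵ = 22.6%.
- Five bands at two sites tested separately: 1 − 0.95¹⁰ = 40.1%.
- Theta and beta only: 1 − 0.95² = 9.8%.

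**3. The same risk with correlated tests.** This was simulated under the null, using the group by time F test for two time points (a one-way F test on change, 3 × 15, df 2 and 42).

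| Between-band correlation (assumed) | At least one of five bands significant |
|---|---|
| 0 | 23% |
| 0.3 | 21% |
| 0.5 | 19% |
| 0.7 | 16% |
| 0.9 | 10 to 11% |

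For ten tests, with band correlation 0 to 0.7 and site correlation 0.5 to 0.9, the result is 21% to 38%.

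**4. Power if all five bands stay primary.** Bonferroni sets 0.05/5 = 0.01 per band, for a family-wise error of 1 − 0.99⁵ = 4.9% if independent. At N = 45 and f = 0.2496:

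| Time points | α = 0.05 | α = 0.01 |
|---|---|---|
| 4 (Sample Size) | 95.5% | 85.6% |
| 2 (Inferential Statistics) | 83.2% | 61.7% |

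Holm tests the smallest p-value at the same 0.01, so the last column is a lower bound for each band's power under Holm.

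**5. Gamma.** The range 30–50 Hz overlaps the omitted 45–60 Hz over 45–50 Hz, which is 5 of 20 Hz or 25% of the band. This does not enter any error rate above.

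**The case against.** The strongest reply is that the alpha sentence is only a default, that no passage says one significant band is enough, and that a multiplicity procedure may stand in a full protocol or analysis plan not shown. The first two parts are correct, and they make the error rate conditional. The third does not remove the gap: a multiplicity rule elsewhere would not supply the primary variable that this text leaves open, and the sample size in this same text is for one test.

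Two further replies limit the point:
- A reader might infer an error rate of 20 to 40%. The documents do not support that range. The 40% needs FP1 and FP2 tested separately and ten independent tests. The article specifies neither, and two frontal channels on a common reference in one person are unlikely to be independent. With strongly correlated bands the rate falls below 20%.
- A reader might also say that no direction exists at all. That goes too far. The Introduction cites a drug-cue direction for every band, so a shift back towards the neutral response is implied, though never stated as the criterion. Two-sided testing is standard and is not itself a fault.

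Nor has the sponsor in effect already chosen beta. The Introduction says only that "increased prefrontal beta activity may serve as a robust indicator of MA craving". The support there is alcohol and smoking cues plus beta synchronization across abstinence groups. The MA-specific VR findings cited concern the other four bands.

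**Conclusion.** The point holds. The primary outcome is a set of five band powers, with no designated band, site summary or multiplicity control, and the sample size is for a single test at 0.05. If any band can count as success, the family-wise error is about 23% for independent bands and about 10 to 21% for correlations of 0.9 to 0.3. Even the lowest of these is about twice the nominal level. The correlations are assumptions, and 40% is a ceiling for ten independent tests, not an estimate.

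The gamma conflict is real but separate and minor. It is tempting to count it towards the false-positive risk, but it adds nothing to it.

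**What to change.** Before unblinding, do one of the following.

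**Option 1: one primary variable.** Keep the plan's own measure: log power, post-dark minus pre-dark, mean of FP1 and FP2, in the MA scene, tested by the group by time (T0, T3) interaction. State the direction expected in the MA VR scene + TBS group relative to the other two groups. State also which MA scene is meant: VR Retrieval shows two at baseline and post-test, while the outcome section counts one. Frontal beta is the candidate the article best supports, though in hedged terms, and the sponsor may justify another band. The remaining four bands become secondary with Holm adjustment. The alpha for the primary test stays at 0.05. The cost is protocol wording, and that a result in another band can no longer be called primary.

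**Option 2: keep all five bands primary** with Holm adjustment and restate the power. At 0.01 it is about 86% with four time points and about 62% with the two in Inferential Statistics (printed f, ρ = 0.5 assumed). A site summary is still needed. The cost is power, or a larger sample.

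**Gamma, separately.** If raw data are available, recompute gamma as 30–45 Hz. Because band powers are computed on the device, rewording alone may not change them. If raw data are not available, state that on-device gamma includes 45–50 Hz affected by the notch filter, and treat gamma as exploratory.
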